### 8.4. Expected adverse events

In this study, as an expected adverse event, falling related to high-intensity interval walking may occur although its risk is low.

## 9. Target number of registered subjects

Target number of registered subjects: 1000

## 10. Statistical matters

### 10.1. Reasons for the establishment of the target number of registered subjects

We will verify that the effects of IWT on physical fitness and age-associated diseases. This is an exploratory study, and the data from previous studies are insufficient. The N value to achieve the detection power “significance level on two-sided tests:  $\alpha \leq 0.05$ ,  $(1-\beta) \geq 0.8$ ” is unclear. Therefore, both the  $\alpha$  and  $(1-\beta)$  values will be described in articles as a reference for additional studies/research.

### 10.2. Statistical analysis

One-way ANOVA for repeated measures is used to examine any significant changes in the variables after training. To examine any influence of covariant factors on the effects of IWT, we use ANCOVA (analysis for covariance) or multiple regression analysis.

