## 4. Study methods

### 4.1. Study design

- Single arm intervention

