## 5.2. Assignment methods and assignment-regulating factors

This is not applicable because this study is single-arm intervention.

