##### 2) Information on training execution

The number of days when training was performed per week, duration of high-intensity walking per day of training, and duration of slow walking are calculated.

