#### 10.3.3. Analysis regarding accessory endpoints

We expect that after the intervention, increases in physical fitness will be accompanied by improvements in age-associated diseases.

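### The stated pre/post test in one uncontrolled arm can show change during the programme, but it cannot verify an effect of IWT or the expected link between fitness and disease

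*Protocol*

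**What the plan says.** The design is described as "Single arm intervention" (Protocol 4.1), and 5.2 says of assignment: "This is not applicable because this study is single-arm intervention". Sections 4.2 and 7 place the outcome measurements before and after training only. The primary outcome in section 6 is peak aerobic capacity (VO2peak) at those two times.

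Section 10.1 states the aim in an incomplete sentence: "We will verify that the effects of IWT on physical fitness and age-associated diseases". The next sentence reads: "This is an exploratory study, and the data from previous studies are insufficient". Section 9 gives "Target number of registered subjects: 1000".

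Section 10.2 gives the main test: "One-way ANOVA for repeated measures is used to examine any significant changes in the variables after training". Its second sentence plans ANCOVA or multiple regression for covariates, which it does not name. Section 10.3 sets two-sided significance at 0.05.

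Section 10.3.2 is headed as hypothesis-verifying but contains only the expectation that fitness and symptoms will improve. Section 10.3.3 expects that "increases in physical fitness will be accompanied by improvements in age-associated diseases". On training, 10.3.1 says that days per week are worked out and that "duration of high-intensity walking per day of training, and duration of slow walking are calculated".

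**The concern.** The aim is causal and the test is not. A mean change from before to after training contains the training effect plus anything else that moves the measurement over the same months. The protocol itself shows some candidates:

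- The fitness test is done once before and once after training, so familiarity with it enters the change.
- Drug treatment may continue during the intervention (4.4), which can move blood pressure, lipids and glucose.
- Registration closes on 30 September 2009 and the study ends on 31 March 2010 (18.1), so the latest registrants would go from about early autumn to late winter.

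Nothing in the stated analysis separates these from IWT. If the paper follows the wording of 10.1 and 10.3.2, a p-value below 0.05 would be reported as a verified effect of IWT.

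Section 10.3.3 raises a second problem. It concerns whether the people who gain fitness are the ones whose disease measures improve. The repeated-measures ANOVA, applied to each variable in turn, does not address that.

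**Working it through.** **Inputs from the protocol.** One arm (4.1, 5.2); two assessments (4.2, 7); 1000 registered (9); two-sided 0.05 (10.3). No effect size, SD, correlation or dropout rate is given, and 10.1 says that the number needed for 80% power is unclear. The figure of 1000 therefore cannot be reproduced, and sizes are given below in units of the SD of individual change.

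**Step 1: what the test is.** With two time points, one-way repeated-measures ANOVA has F = t² on 1 and n − 1 degrees of freedom, where t is the paired t statistic. On a simulated data set of 1000 pairs both gave 18.73. The null hypothesis is zero mean change.

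**Step 2: how much drift it detects.** Let d be a mean change unrelated to training, divided by the SD of change, and suppose that there is no training effect.

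- Smallest observed change that is significant: t(0.975, 999)/√1000 = 1.962/31.62 = 0.062 SD.
- Drift significant 80% of the time: (1.960 + 0.842)/31.62 = 0.089 SD.
- Chance of significance, from the noncentral t with noncentrality d√n:

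| Drift d | n = 1000 | n = 800 (assumed) | n = 500 (assumed) |
|---|---|---|---|
| 0.05 | 35% | 29% | 20% |
| 0.10 | 88.5% | 81% | 61% |
| 0.15 | 99.7% | 99% | 92% |

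The columns for 800 and 500 allow for incomplete pairs, because 1000 is a registration target. In between-person SD units, multiply d by √(2(1 − ρ)), where ρ is the pre/post correlation. For an assumed ρ of 0.5 to 0.9, a drift of 0.10 SD of change is 0.10 to 0.045 between-person SD.

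Drift can run either way. A favourable one would be read as an effect, and an unfavourable one would mask one.

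**Step 3: the link in 10.3.3.** A test of mean VO2peak change uses the mean and variance of that change. A test of mean change in a disease measure uses the mean and variance of that measure's change. Neither uses the covariance between the two. Both can be significant when the individual changes are uncorrelated, so two such results say nothing about whether one accompanies the other.

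**Step 4: what the recorded training could add.** In 2000 simulated trials of 1000 people, with a uniform drift of 0.10 SD and dose unrelated to change, the pre/post test rejected in 88.6% and a test of the dose slope in 5.1%. The dose correlation detectable with 80% power is tanh(2.802/√997) = 0.088. A dose slope is therefore insensitive to drift that is the same for everyone. It is not protected against drift that is related to dose.

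**The case against.** The strongest reply is that the protocol hides nothing. It declares a single arm and calls itself exploratory, and lack of a control group is a known limit of such a design. The sentence in 10.1 is incomplete and may be no more than loose wording. Section 10.2 already plans regression, and choosing its covariates is commonly left to a statistical analysis plan. Much of this stands, and it limits the point to what the stated test can support. The word *verify* and the heading of 10.3.2 remain at odds with the exploratory label.

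Four stronger readings are tempting, and the documents do not support them.

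- *Almost any drift would be declared an effect.* At 0.05 SD the test misses about 65% of the time even with 1000 pairs. The underlying problem is bias from having no comparator; the large sample only makes moderate bias significant.
- *The training record is merely tabulated.* Section 10.3.1 says that the quantities are calculated, and the unnamed covariates in 10.2 could include them. One can say only that no stated analysis names them.
- *Regression to the mean inflates the result.* This would matter for people picked out by a high pre-training reading, but no such analysis is planned, and eligibility (3.1, 3.2) sets no VO2peak threshold.
- *A dose slope would prove the effect.* Participants choose how much they walk. Section 4.2 also fixes high intensity relative to pretraining VO2peak, so someone who becomes fitter for any reason can log more high-intensity minutes.

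The seasonal argument is limited too. The registration opening date is not stated, so neither the size nor the direction of a seasonal shift across the cohort can be derived.

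**Conclusion.** The point holds in a limited form. The stated primary analysis supports a statement about change over the programme, not verification of an IWT effect. With 1000 complete pairs, a non-training drift of about 0.1 SD of change would be significant about 88% of the time; with 500 pairs (assumed), about 61%. The protocol gives no estimate of the actual drift, so these figures show what the test would do with such a drift, not that one will occur. Nor do they suggest that IWT has no effect.

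Separately, none of the stated models ties disease change to individual fitness change, so tests of mean change would leave the expectation in 10.3.3 untested. An analysis plan that is not shown might supply such a model. The severity is below must-fix: the design is openly declared, and the repair is mainly to the claim and to the named regression terms.

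**What to change.** 1. **Sections 10.1 and 10.3.2.** State the primary result as the mean change in VO2peak from before to after the programme, with a 95% confidence interval. Remove the language of verifying an IWT effect, including from the heading of 10.3.2.
2. **Section 10.3.3.** Regress each post-training disease measure on its own baseline, the individual VO2peak change, age and sex (logistic form where the measure is yes/no). Report the VO2peak coefficient with its interval as an association.
3. **Section 10.2.** In the regression of post-training VO2peak, name recorded high-intensity walking time as a term, with baseline VO2peak, age, sex and date of assessment. Present the dose coefficient as supportive observational evidence only, and give both reasons: dose is self-selected, and the intensity threshold is set on pretraining VO2peak.

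The cost is a more modest claim and a little more analysis. All the data are already to be collected. None of this replaces a control group: changes in drug treatment and differences in motivation can still lie behind the associations in items 2 and 3.

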### 10.3. Analytical items/methods

An outline of statistical analysis is shown below. A p-value of 0.05 is regarded as significant (two-sided test).

#### 10.3.1. Outline of subjects to be analyzed

##### 1) Subjects' background factors and baseline data

Subjects' physical properties and physical fitness before training should be adopted as baseline data.

##### 2) Information on training execution

The number of days when training was performed per week, duration of high-intensity walking per day of training, and duration of slow walking are calculated.

#### 10.3.2. Hypothesis-verifying analysis regarding primary endpoints

After training intervention, increases in physical fitness and improvements of age-associated disease symptoms can be expected.

#### 10.3.3. Analysis regarding accessory endpoints

We expect that after the intervention, increases in physical fitness will be accompanied by improvements in age-associated diseases.

### 11. Entry/submission of case reports

#### 11.1. Form and deadline for submission

The "case report" form is attached. The deadline for submission is 1 week after the final day of intervention.

#### 11.2. Cautions for filling in case reports

When filling in case reports, please comply with the following matters:

- 1) Case reports should be written using a black or blue ballpoint pen or pen.
- 2) In a blank column, a diagonal line should be drawn to distinguish it from an "omission".
- 3) Before submission, consistency with original materials, such as medical records, must be confirmed.
- 4) When changing or revising descriptions, the corresponding part should be deleted with

a double line, and correct matters should be written. The investigator responsible for revision must affix a seal or sign the paper with the date.

- 5) A seal to be used when writing case reports should be unified in each patient.

## 12. Monitoring

According to the procedure manual for monitoring (including the monitoring plan) prepared by the study director, the monitor should confirm that subjects' human rights, safety, and welfare are protected, that this study is conducted in accordance with the latest protocol, "Ethical Guidelines for Medical and Health Research involving Human Subjects", that the data obtained are accurate and complete, and that they can be verified in the context of relevant records, such as medical records. Actual operations will be conducted by [name], Department of Sports Medical Sciences, Shinshu University Graduate School of Medicine.

## 13. Audit

As this is a single arm exploratory study, an audit will not be performed.

## 14. Ethical matters

### 14.1. Regulations to be observed

The persons concerned in this study must observe the "Declaration of Helsinki" by the World Medical Association and "Ethical Guidelines for Medical and Health Research involving Human Subjects".

### 14.2. Informed consent

The investigators must hand over an explanatory document for obtaining informed consent approved by the Ethics Review Board of our university to subjects, explain the contents using the document and verbally, and obtain written informed consent based on subjects' free will.

When information that may influence subjects' consent is obtained, or when there is a change of the protocol that may influence subjects' consent, the investigators must promptly provide information to subjects, and confirm their will for study participation. In addition, they should revise the explanatory document for obtaining informed consent through approval by the Ethics Review Board of our university, and obtain additional

consent from subjects.

The explanatory document should contain the following contents:

- ① Study name and permission from the director of a research institute regarding the execution of the corresponding study
- ② Research institute's name and study director's name (including the names of collaborative research institutes and names of the study directors of these institutes when the study is conducted in collaboration with other research institutes)
- ③ Purpose and significance of the study
- ④ Study methods (including the purpose of utilizing samples/information obtained from study subjects) and period
- ⑤ Reasons for the selection of study subjects
- ⑥ Subjects' burdens, expected risks/advantages
- ⑦ Even when subjects agree to study execution or continuation, they can withdraw from the study at any time (when it is difficult to take measures in accordance with the contents of withdrawal from study subjects, the contents and reasons must be explained).
- ⑧ Even when subjects do not agree to study execution or continuation, or even when they withdraw from the study, there will be no disadvantage for subjects.
- ⑨ Methods to disclose information on research
- ⑩ Subjects can obtain or inspect the protocol and materials regarding study methods in a range in which there is no problem for protecting other subjects' personal information and securing the originality of the study based on their requests.  
Methods to obtain or inspect them.
- ⑪ Handling of personal information (for anonymization, its methods are included).
- ⑫ Storage and abolishment of samples/information
- ⑬ Status of the research-related conflict of interest for research institutes, such as funding sources, and that for investigators, such as personal income
- ⑭ Management of consultations from the subjects and persons concerned
- ⑮ Contents of financial burdens or rewards for subjects (if such matters are present)
- ⑯ Presence or absence and contents of compensations for health damage related to the corresponding study in the case of invasive research
- ⑰ The samples/information obtained from subjects may be used for future research that is not specified on obtaining informed consent from subjects, or provided to

other research institutes (if there is such a possibility). Contents expected on obtaining informed consent.

- ⑱ On the assumption that subjects' secrets may be kept, persons engaged in monitoring/audit and review-board members may inspect samples/information regarding the corresponding subjects in a necessary range.

#### 14.3. Protection of personal information

When handling information regarding study execution, a correspondence table should be prepared by attaching a number that is not related to the subject's personal information, and anonymization should be conducted so that subjects' secrets may be protected. The correspondence table must be strictly managed by a personal information administrator, and should not be provided to external organizations. When publishing the study results, attention must be paid so that information that allows the identification of subjects may not be included. Furthermore, the subject information obtained in the study should not be used for purposes other than the study purpose.

#### 14.4 Storage of samples/information

Information (materials) regarding this study (documents on research and study data) must be stored in a lockable storage apparatus in the Shinshu University Graduate School of Medicine for 10 years after outcome presentation, such as article publication, under the direction of a person responsible for management (study director). After the completion of the storage period, anonymized paper data should be discarded using a shredder. Electronic data should be completely deleted.

#### 15. Recording matters regarding the provision of samples/information

As there is no transfer of samples/information, records will not be prepared.

#### 16. Change of the study protocol

If the protocol of this study or explanatory document for obtaining informed consent is changed or revised, this must be initially approved by the Ethics Review Board of our university.

## 17. Research expenses

### 17.1. Research funds and conflict of interest

This study will be conducted with the grant from the Ministry of Health, Labor and Welfare of Japan. Furthermore, investigators participating in this study must report necessary matters to the industry-academia collaboration conflict of interest management committee of Shinshu University according to the “Shinshu University School of Medicine procedures for ethical review application” so that the contents may be inspected and approved.

### 17.2. Subjects’ cost allocation or rewards

This study will be supported by the grant above and participants will not pay any costs for this study.

### 17.3. Management of health damage and compensations

If health damage occurs in subjects during this study, investigators must provide adequate treatment. Furthermore, compensations for health damage should be paid according to the “Ethical Guidelines for Medical and Health Research involving Human Subjects”. There may be no fatal, severe adverse events; therefore, there will be no problem if insurance is not established. Thus, in this study, no monetary compensations for subjects’ health damage are prepared. This will be approved by the Ethics Review Board of our university, and sufficiently explained to subjects. We will ask them to participate in this study based on their understanding and consent.

## 18. Study period and the completion/early discontinuation of this study

### 18.1. Study period

Subject registration period: Date of approval–September 30, 2009

Study period: Date of approval–March 31, 2010

### 18.2. Completion of this study

When measurement is completed, this study will be completed. The study director will promptly submit a report on study completion to the head of the School of Medicine.

### 18.3. Early discontinuation of this study

The investigators should examine whether study execution/continuation is possible when the following matters are met.

- 1) When it is considered extremely difficult to reach a target number of patients due to difficulties in subject incorporation
- 2) When the study purpose is achieved before a target number of patients or intended period is reached
- 3) When there may be problems regarding safety based on safety information such as reports on severe adverse events
- 4) When adequate study continuation is considered to be difficult due to deviations from the ethical guidelines/study protocol or contract violations
- 5) When it is considered difficult to accept a direction for a change of the protocol from the Ethics Review Board of our university

The study director should discontinue this study if discontinuation is recommended or directed by the Ethics Review Board of our university. If study discontinuation is determined, the study director must promptly report this and its reasons in writing to the head of the School of Medicine.

### 19. Storage of medical instruments, usage, and storage period

Personal management will be thoroughly conducted by attaching a number so that there may be no misuse, reforming, or misunderstanding of a portable calorie meter to be delivered to each subject.

### 20. Storage of records

The study director must store important documents regarding study execution (a copy of the application form, notifications from the hospital director, copies of various applications/reports, informed consent, and other documents or records necessary to assure the data reliability) for 10 years after outcome presentation, such as article publication. Subsequently, these documents should be discarded, paying attention to personal information.

### 21. Attribution of the study outcome

The outcome of this study belongs to Shinshu University. The study director will publish

the outcome of this study through presentations at relevant society meetings.

